## Abstract

**Background:**

Cryptogenic stroke (CS) are heterogeneous in origin; however, most CS are embolic mechanism. Paroxysmal atrial fibrillation (AF) is suspected to be a major type of CS that leads to severe cerebral infarction without anticoagulant use. Therefore, the identification of AF is vital in patients with CS. However, patients are often unaware of AF because they have no symptoms, and AF may not be detected on an electrocardiogram (ECG) or Holter ECG on admission. After patients with stroke are treated in the acute phase, they are promptly transferred to a rehabilitation hospital for functional recovery. Once the patient is transferred to a hospital, a few attempts are made to detect AF. In addition, rehabilitation therapists are considered to have insufficient awareness of the possibility of undiagnosed AF.

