**Methods:**

This multicenter prospective observational study aimed to detect AF in patients with non-cardiac stroke at rehabilitation hospitals. Therapists performed pulse checks before, during, and after rehabilitation. If arrhythmia or tachycardia was detected, an ECG was performed, and the physician checked for AF. If the patient complained of chest symptoms, electrocardiography (ECG) was performed to check for AF. We investigated the characteristics, laboratory data, cognitive status, complications, such as stroke recurrence, and functional outcomes of patients with AF.

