### Evaluations and follow-up

2.4.

The following parameters were evaluated: (1) feasibility of pulse checks in rehabilitation hospitals, (2) proportion of AF detection, and (3) proportion of initiation of anticoagulant therapy. Patients usually undergo rehabilitation therapy 3 times daily at rehabilitation hospitals. Trained rehabilitation staff performed pulse checks for each patient before, during, and after rehabilitation (9 times daily). If an irregular pulse and tachycardia (heart rate of 120 beats/min or faster) were detected, a 12-lead ECG immediately (within 5 min) after pulse assessment was essential to confirm or rule out AF (Figure 1). For patients with identified AF, the prescription will be changed to an anticoagulant at the rehabilitation hospital and the study office will be contacted. If the attending physician at the rehabilitation hospital has concerns about the prescription, the study office will consult about the prescription. The duration of the regular pulse monitoring is all periods from obtaining consent to admission in rehabilitation hospital.

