### Data analysis plan

2.7.

We will examine the proportion of patients with AF detected, timing of detection, and characteristics of patients with AF. Clinical characteristics such as sex, age, laboratory data, echocardiography data, and brain imaging data, and outcomes will be compared between the patients in the AF and non-AF group. Sub-group analyses will be planned for patients who used other long-term electrocardiographic monitors, such as ICM. All statistical analyses will be performed using the SPSS software (version 27; SPSS Japan, Inc., Tokyo, Japan). The results will be considered statistically significant at *p* < 0.05. Univariate analyses will be performed using *χ*^2^ and Mann–Whitney *U* tests, as appropriate. Data will be presented as medians and interquartile ranges. Categorical variables will be presented as frequencies and percentages.

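### Apart from patients with chest symptoms or a long-term monitor, a normal pulse check has no stated rhythm verification and a negative ECG is read as excluding AF, so the 'non-AF' group holds unknown undetected AF and yield alone cannot show how well pulse checks work

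*Protocol article*

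**What the plan says.** - **Trigger for an ECG.** Section 2.4 of the Protocol article: "If an irregular pulse and tachycardia (heart rate of 120 beats/min or faster) were detected", a 12-lead ECG follows. The Abstract (Methods) has a different connective: "If arrhythmia or tachycardia was detected, an ECG was performed, and the physician checked for AF". The Abstract adds a second route: "If the patient complained of chest symptoms, electrocardiography (ECG) was performed to check for AF". The text of section 2.4 does not mention this second route.
- **Reading of the ECG.** Section 2.4 says the ECG "immediately (within 5 min) after pulse assessment was essential to confirm or rule out AF". The article states no further step after a negative ECG, although pulse checks continue at nine a day.
- **Groups analysed.** Section 2.7: clinical characteristics and "outcomes will be compared between the patients in the AF and non-AF group".
- **Long-term monitors.** Section 2.3 admits patients with an insertable cardiac monitor (ICM). Section 2.7: "Sub-group analyses will be planned for patients who used other long-term electrocardiographic monitors, such as ICM". The purpose of that analysis is not given, nor is it said whether AF found only by a monitor counts towards the detection proportion.
- **The article's own premise.** The Abstract (Background) warns that "AF may not be detected on an electrocardiogram (ECG) or Holter ECG on admission". The Introduction repeats this for paroxysmal AF, and the Discussion calls AF after non-cardiac stroke often asymptomatic and paroxysmal, so that symptom-driven strategies are unlikely to find it.

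**The concern.** Verification by ECG depends on the result of the test under study, or on symptoms that the article considers a poor guide. Two kinds of patient can have AF and still be analysed as non-AF: those whose paroxysms never coincided with an abnormal check, and those with an abnormal check whose paroxysm ended before the ECG. The second kind are suspected cases, yet they sit in the comparator.

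Two aims are affected. The Introduction and Discussion want to establish whether regular pulse checks are useful. The detection proportion is prevalence multiplied by sensitivity, so a low figure could mean little AF or a poor screen, and these lead to opposite conclusions. The Objective also wants the characteristics of patients with AF. What the study will describe is AF that a pulse check can catch.

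**Working it through.** **Figures in the plan.** The only relevant figure is the sample size of 1000 (section 2.6), a count of expected admissions. The article gives no expected AF rate, sensitivity or precision, so there is no calculation to reproduce. Everything below except N = 1000 is an assumption, used to show size.

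**Step 1: what a given yield implies.** Let π be the share of patients with AF at some time during the stay, and s the sensitivity of the whole pathway (pulse check plus ECG). Assume that AF confirmed on ECG is always true AF.

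- Yield y = π × s, so π = y / s.
- Missed cases = N(π − y).
- Missed share of the non-AF group = (π − y) / (1 − y).

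With y = 3% (30 of 1000; exact 95% CI 2.0% to 4.3%), the non-AF group has 970 patients:

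| s | π = 0.03/s | Missed per 1000 | Share of non-AF group |
|---|---|---|---|
| 75% | 4% | 10 | 10/970 = 1.0% |
| 50% | 6% | 30 | 30/970 = 3.1% |
| 25% | 12% | 90 | 90/970 = 9.3% |

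The same 3% yield also fits prevalence and sensitivity of 3% and 100%, 5% and 60%, 10% and 30%, or 20% and 15%. The confidence interval for the yield carries none of this uncertainty.

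**Step 2: effect on the group comparison.** Take a characteristic present in 60% of true AF and 40% of true non-AF, and assume missed cases resemble detected ones. If m is the missed share of the non-AF group, the observed difference is 20 × (1 − m) points.

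| π | s | AF detected | Missed | m | Observed difference | Power, two-sided 0.05: s = 100% → this s |
|---|---|---|---|---|---|---|
| 5% | 50% | 25 | 25 | 25/975 = 2.6% | 19.5 | 80% → 50% |
| 10% | 30% | 30 | 70 | 70/970 = 7.2% | 18.6 | 97% → 53% |
| 20% | 30% | 60 | 140 | 140/940 = 14.9% | 17.0 | 99.9% → 73% |

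The difference itself barely moves. Power falls mainly because fewer AF cases are found (in the second row, 30 instead of 100). No relabelling changes that.

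**Step 3: what a monitored subgroup could deliver.** Its size is not stated. Suppose the monitor documents AF in n patients and pulse checks caught x = n/2. The exact (Clopper-Pearson) limits are the 2.5% quantile of Beta(x, n − x + 1) and the 97.5% quantile of Beta(x + 1, n − x):

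- 5/10: 19% to 81%
- 10/20: 27% to 73%
- 15/30: 31% to 69%

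**Step 4: the trigger passages side by side.** Section 2.4 joins irregular pulse and tachycardia with 'and'; the Abstract joins arrhythmia and tachycardia with 'or'. Read literally, section 2.4 leaves an irregular pulse below 120/min without an ECG and so enlarges the unverified group. The Abstract's wording does not.

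**The case against.** A reader might infer that patients with normal pulse checks never get an ECG. The article does not support that: the Abstract gives chest symptoms as a separate route, and Table 2 lists ECG measurements among the study data without limiting them to triggered patients. A reader might also infer that one negative ECG settles a patient's status for good. It does not: nine checks a day can trigger further ECGs. The passages on missed AF concern the ECG or Holter on admission, not an ECG taken within minutes of an abnormal pulse. All of this stands and narrows the point. It does not close it. By the article's own account the symptom route reaches few paroxysmal cases, repeat ECGs help only if a later check is again abnormal, and no timing or diagnostic use is given for the ECG data in Table 2.

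Detection yield is also a legitimate endpoint. The plan does not claim to estimate prevalence or sensitivity, and usefulness can partly be judged from AF found and anticoagulation started. That stands too: the yield is valid as a yield. It cannot by itself say how well the test performs.

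Finally, an article may leave the content of the ICM subgroup to a fuller document, so its absence is no error. The point rests on what the article does fix: the meaning of a negative ECG and the name of the comparator.

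**Conclusion.** The point holds in limited form. Patients without chest symptoms or a long-term monitor whose pulse checks stay normal have no stated rhythm verification. A negative ECG after a positive check is taken to exclude AF, against the article's own premise. The non-AF group therefore contains an unknown number of undetected AF cases.

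The larger consequence is for interpretation: at an assumed 3% yield, sensitivities of 75% to 25% imply a threefold range of true AF, 4% to 12%. It would be tempting to conclude that the AF versus non-AF comparison is seriously biased. The figures do not support that: in the scenarios shown, dilution takes about 1% to 15% off a difference, provided missed cases resemble detected ones. If AF that pulse checks miss differs in kind, the characteristics reported describe only detectable AF, and this arithmetic does not capture that.

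The yield and sensitivities are assumptions; none is in the document. This is a worthwhile, inexpensive improvement, not a fatal flaw.

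**What to change.** In section 2.7:

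1. In the planned ICM/long-term-monitor subgroup, cross-tabulate pulse-check detection against monitor-documented AF. Report sensitivity with an exact 95% CI, and report AF found only by the monitor separately from the pulse-check yield.
2. Record 'positive pulse check, AF not on ECG' as its own category, and repeat the group comparison with these patients removed from the comparator.
3. Label the groups 'AF detected' and 'AF not detected', and limit conclusions on characteristics to AF that pulse checks can detect.

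Separately, reconcile the ECG trigger in section 2.4 with that in the Abstract, including whether chest symptoms are a route.

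**Cost.** Two data items (monitor result; pulse-positive, ECG-negative status), which Table 2 does not list, and some analysis wording. No extra procedure. Recruitment was due to end in August 2023, so the items may have to come from site records. The sensitivity estimate would come from a selected and possibly small subgroup and could be too wide to settle the question, as 5/10 with 19% to 81% shows. Items 2 and 3 do not depend on its size. Item 3 alone would be mostly editorial.

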**Figure 1 fig1:**
[figure not shown]
Study flowchart. This flowchart illustrates the design of this study. It shows the flow chart from stroke diagnosis at the stroke center to pulse and AF diagnosis at the rehabilitation hospital. AF, atrial fibrillation.

### Data collection

2.5.

The following study data will be encrypted and stored on a website: patient characteristics, electrocardiogram data, laboratory data, hospital events, and discharge status (Table 2). The data will be accessible only to study researchers with appropriate training and ethics review board approval, and the study steering committee will independently monitor the data.

**Table 2 tab2:** Detailed survey in this study.

**Patient characteristics**
Age, sex, height, weight, modified Rankin Scale (mRS) score, type of stroke, hypertension, dyslipidemia, diabetes mellitus, chronic kidney disease, congestive heart failure, cerebrovascular disease, peripheral artery disease, peripheral artery disease, thromboembolism, active cancer, dementia, alcohol intake, smoking, antithrombotic therapy, functional independence measure (FIM), and mini mental state examination stroke (MMSE)
**Electrocardiogram**
PR interval, QTc interval, and supraventricular extrasystole
**Blood examination**
Routine blood biochemistry examinations, including creatinine clearance, blood glucose, low-density lipoprotein cholesterol and measurements of D-dimers, brain natriuretic peptide (BNP), and N-terminal prohormones of the BNP
**Events in the hospital**
Infection (urinary tract infection, pneumonia, cholecystitis, and other), recurrent stroke, falls
**Status at discharge**
mRS at discharge, MMSE at discharge, FIM at discharge, and discharge destination (home, hospital, convalescent home, other)

### Sample size

2.6.

Notably, this study has not been previously reported. The number of possible participants in the study in a year was calculated from the number of admissions at participating facilities in the previous year and set at 1000.

### Data analysis plan

2.7.

We will examine the proportion of patients with AF detected, timing of detection, and characteristics of patients with AF. Clinical characteristics such as sex, age, laboratory data, echocardiography data, and brain imaging data, and outcomes will be compared between the patients in the AF and non-AF group. Sub-group analyses will be planned for patients who used other long-term electrocardiographic monitors, such as ICM. All statistical analyses will be performed using the SPSS software (version 27; SPSS Japan, Inc., Tokyo, Japan). The results will be considered statistically significant at *p* < 0.05. Univariate analyses will be performed using *χ*^2^ and Mann–Whitney *U* tests, as appropriate. Data will be presented as medians and interquartile ranges. Categorical variables will be presented as frequencies and percentages.

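### AF yield, timing and patient characteristics are analysed with no allowance for days monitored, although monitoring lasts for an open-ended rehabilitation stay; if stays differ, characteristics tied to longer stay can appear tied to AF

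*Protocol article*

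**What the plan says.** Evaluations and follow-up (2.4) sets the intensity of monitoring: "Trained rehabilitation staff performed pulse checks for each patient before, during, and after rehabilitation (9 times daily". It then defines the duration: "The duration of the regular pulse monitoring is all periods from obtaining consent to admission in rehabilitation hospital". No number of days is given. The end point cannot be meant literally, because the checks are done by staff of the rehabilitation hospital during therapy there, that is, after admission.

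Data analysis plan (2.7) lists the targets: "We will examine the proportion of patients with AF detected, timing of detection, and characteristics of patients with AF". It adds that clinical characteristics and "outcomes will be compared between the patients in the AF and non-AF group". The tests are named: "Univariate analyses will be performed using *χ*^2^ and Mann–Whitney *U* tests, as appropriate". The summaries are named too: "Data will be presented as medians and interquartile ranges", with frequencies and percentages for categorical variables. The significance level is 0.05.

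No rate per patient-day, censoring rule, common time window or adjustment for days monitored is stated. Table 2 lists several items of status at discharge, but no dates of first check, AF detection or end of monitoring, and no count of checks performed.

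**The concern.** A patient checked nine times a day for 90 days receives three times as many checks as one who stays 30 days. Whether a patient falls in the AF or the non-AF group therefore depends on how long that patient was watched as well as on whether AF was present. The stated methods treat ever-detected status as if everyone had been watched equally.

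Three results are exposed. The proportion with AF detected has no time horizon, so it cannot be compared with other cohorts or other lengths of monitoring. Detection times can be observed only up to the end of monitoring, so their summary depends on how long people stay. In the group comparison, a characteristic associated with longer stay can appear associated with AF when it is not. The rate and timing of detection and the characteristics of patients with AF are declared aims in the Objective, so this touches the main results.

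The timetable may add to the inequality. Results (3) has recruitment ending in August 2023 and analyses complete by the same month, so late enrolees may be cut off before their stay ends.

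**Working it through.** **Figure in the plan.** The sample size of 1000 is a count from the previous year's admissions. It has no statistical inputs, so there is nothing to reproduce.

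**Inputs.** From the article: n = 1000, significance level 0.05 (two-sided assumed), χ² on ever-detected status. Assumed, because the article gives none of them: daily detection hazard λ = 0.0005, half the patients in each of two stay lengths, and a yes/no characteristic with no effect on AF but more common among long-stay patients. Linkage 80/20 means that 80% of long-stay and 20% of short-stay patients have the characteristic.

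**Step 1: yield by stay, same hazard in everyone.** P(detected by day t) = 1 − exp(−λt).
- 30 days: 1 − exp(−0.015) = 1.49%
- 60 days: 1 − exp(−0.030) = 2.96%
- 90 days: 1 − exp(−0.045) = 4.40%

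For 90 against 30 days the odds ratio is (0.0440/0.9560)/(0.0149/0.9851) = 3.05, from exposure alone. Expected detections are 500 × 0.0149 + 500 × 0.0440 ≈ 29, a yield of about 3%.

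**Step 2: what passes to the characteristic.** With 30 and 90 days and 80/20 linkage:
- with it: 0.8 × 4.40 + 0.2 × 1.49 = 3.82%
- without it: 0.2 × 4.40 + 0.8 × 1.49 = 2.07%
- apparent odds ratio: about 1.9

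With 60 and 90 days and 60/40 linkage:
- with it: 0.6 × 4.40 + 0.4 × 2.96 = 3.82%
- without it: 0.4 × 4.40 + 0.6 × 2.96 = 3.54%
- apparent odds ratio: about 1.1

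**Step 3: how often χ² gives p < 0.05 for this null characteristic** (simulation, thousands of trials per row; repeat runs agree to within one or two percentage points).

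| Stays (days) | Linkage | Hazard | χ² false positives |
|---|---|---|---|
| 60 vs 90 | 60/40 | constant | about 5% |
| 60 vs 90 | 80/20 | constant | about 12% (10% with average yield held at about 3%) |
| 30 vs 90 | 60/40 | constant | about 9% |
| 30 vs 90 | 70/30 | constant | about 19% |
| 30 vs 90 | 80/20 | constant | about 37% |
| 30 vs 90 | 80/20 | front-loaded (Weibull shape 0.5) | about 13% |

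Doubling the hazard to 0.001 raises the 37% row to about 63%. A log-rank test on time to detection, censored at the end of the stay, rejects in about 5% throughout. With equal stays χ² is also near 5%. In these simulations stay is unrelated to AF hazard, which is the condition under which censoring at its end is valid.

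**Step 4: timing.** The median m among those detected solves 1 − exp(−λm) = ½[1 − exp(−λt)]. For stays of 30, 60 and 90 days this gives 14.9, 29.8 and 44.5 days. With a low front-loaded hazard of shape 0.5, √(m/t) = ½, so m = t/4: about 7.5, 15 and 22.5 days. In both cases the median moves with the stay although the hazard is common to all, but its level depends on the shape of the hazard.

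**The case against.** **Condensed article.** This is a journal article without its full analysis plan, and naming two tests for univariate analyses does not exclude a time-to-event or adjusted analysis elsewhere. That is right as far as it goes. But the article carries its own analysis section, which fixes tests, summaries, software and significance level. The point concerns the methods it names for its declared aims.

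**The proportion is legitimate.** Yield per admission is a sensible quantity for judging whether pulse checks are feasible and useful during a rehabilitation stay. This stands, and the proportion should be kept as a descriptive result.

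**The size rests on assumptions.** The article gives no length of stay, spread of stay, AF rate or link between stay and any characteristic. This stands as well, and mild inputs leave the error rate at about its nominal level.

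**Stronger readings.** A reader might infer that age, disability or dementia will emerge as false risk factors because such patients stay longer. The article does not say that stay follows these variables, and it promises characteristics of patients with AF, not risk factors. A reader might also infer that timing will be reported as a median among detected patients. The line on medians is a general one, and no method is given for timing in particular. Finally, a reader might infer that the median would reflect only the stay, whatever the course of AF. Step 4 shows otherwise: the shape of the hazard changes it by a factor of two.

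**Conclusion.** The point holds in conditional form. The article describes monitoring of open-ended and unclearly bounded duration and names no method that accounts for it. If stays differ, the yield has no time horizon and detection times are truncated at the end of monitoring. If stays also differ by a characteristic, that characteristic can appear associated with AF.

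For about 3% yield in 1000 patients, the chance of a false χ² result runs from about 5% to about 37%, with 12–19% for intermediate inputs and about 13% in the strongest case if detection is front-loaded. The stays, hazard and linkage are all assumptions, and the bias is nil if stays are equal or unrelated to the characteristic. The article therefore supports saying that the planned comparisons can mislead, not that they will. The change is worth making because it is cheap and bears on the declared aims.

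**What to change.** 1. Reconcile the monitoring window in Evaluations and follow-up with the description of checks during the rehabilitation stay, and state when monitoring starts and ends. No censoring rule can work until this is done.
2. Add to Table 2 the dates of first check, AF detection and end of monitoring.
3. Keep the per-admission proportion as a descriptive yield. Add the cumulative incidence of AF detection by day with 95% CI, censored at end of monitoring with death as a competing event, and detections per 1000 patient-days. Detections per 1000 checks is optional, and only if check counts are recorded.
4. Describe timing by the cumulative incidence curve.
5. Compare baseline characteristics by log-rank or Cox regression on time to detection, in place of χ² and Mann–Whitney on ever-detected status. State the assumption that the end of monitoring is unrelated to AF hazard, given the characteristics in the model.

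The cost is three dates per patient and slightly more analysis, so it is more than a change of wording. Whether those dates are already held is not stated.

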**Objective:**

This study aimed to increase the understanding of the importance of AF detection in patients with ischemic stroke among therapists in rehabilitation hospitals and to investigate whether regular pulse screening can aid in the detection of AF. If AF was detected, we determined the rate and timing of AF detection and identified the patient characteristics.

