## Introduction

1.

Approximately 15%–40% of all ischemic strokes are characterized as cryptogenic stroke (CS) (1). CS are heterogeneous in origin; however, many CS are thought to exhibit embolic mechanisms. Paroxysmal atrial fibrillation (AF) is suspected to be the major cause of CS. AF attributable to large- or small-vessel disease has also been reported in stroke patients (2).

The number of patients with AF increases with age (3, 4); however, AF is sometimes difficult to detect. AF is classified as persistent AF if it lasts for more than 1 week or as paroxysmal AF if it disappears within 1 week. Paroxysmal AF is sometimes unrecognized by patients because it is asymptomatic (5) and may not be detected on electrocardiography (ECG) or Holter ECG examination on admission.

Paroxysmal and persistent AF are associated with a high risk of recurrence without anticoagulant therapy (6); therefore, we treated the patients with anticoagulant therapy to prevent stroke due to AF. Current Japanese guidelines for stroke recommend that stroke in which AF is not detected should be classified as non-cardiogenic stroke and treated with antiplatelet agents (aspirin, clopidogrel, prasgrel, and cilostazol) to prevent recurrence. However, when atrial fibrillation is observed, antiplatelet drugs are insufficient to prevent stroke recurrence, and anticoagulants (warfarin, dabigatran, rivaroxaban, apixaban, edoxaban) are more effective in preventing recurrence (7, 8). Therefore, it is important to actively identify patients with stroke without AF.

Recently, stroke care has changed considerably with advances in acute therapy and shortened length of hospitalization. Once patients are transferred to a rehabilitation hospital, fewer attempts are made to detect AF. In addition, rehabilitation therapists have insufficient awareness of the possibility of undiagnosed AF and the importance of AF detection. In this study, we aimed to increase the understanding of the importance of AF detection among therapists in rehabilitation hospitals and investigate whether regular pulse screening can aid in the detection of AF. If the feasibility and usefulness of regular pulse testing during rehabilitation are confirmed, the detection of AF after stroke can be recommended.

This study also aimed to clarify the rate and timing of AF detection by performing pulse testing.

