### Patient population

2.3.

Patient enrollment for this ongoing study began in September 2022 at six medical partner institutions in Tokyo, Japan. The inclusion criteria were as follows: (1) patients diagnosed with non-cardiogenic stroke, (2) patients aged >20 years, and (3) patients or their families who agreed to participate in the study and provided informed consent. Patients with insertable cardiac monitor (ICM) were also participated if they met the inclusion criteria. The exclusion criteria were as follows: (1) patients who are currently participating or will participate in another intervention trial, (2) patients with AF or atrial flutter, (3) patients diagnosed with less than 1 year to live, and (4) patients judged by their doctor to be ineligible to participate in the study. A full description of the inclusion and exclusion criteria is presented in Table 1. Trained stroke rehabilitation nurses and physicians educated the registered patients on pulse palpation according to a standardized protocol that focuses on evaluating the heart rate and rhythm regularity. First, rehabilitation therapists were educated about the health implications of AF (i.e., the risk of ischemic stroke, thromboembolism, heart failure, and mortality), clinical presentation, and its frequent asymptomatic nature. The potential health benefits of the intervention were also explained.

**Table 1 tab1:** Inclusion and exclusion criteria.

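### The AF detection proportion is not restricted to, or split by, route of detection, so it cannot identify what pulse checks yield and may overstate it

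*Protocol article*

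**What the plan says.** The Objective in the Abstract is "to investigate whether regular pulse screening can aid in the detection of AF". The Introduction ties the result to the method: "This study also aimed to clarify the rate and timing of AF detection by performing pulse testing".

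The outcome itself names no route. Evaluations and follow-up (2.4) lists it as "2) proportion of AF detection", and the Data analysis plan (2.7) says "We will examine the proportion of patients with AF detected, timing of detection, and characteristics of patients with AF".

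The article describes other ways in which AF can come to light in the same patients:

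- Patient population (2.3): "Patients with insertable cardiac monitor (ICM) were also participated if they met the inclusion criteria".
- Abstract, Methods: "If the patient complained of chest symptoms, electrocardiography (ECG) was performed to check for AF".
- Data analysis plan (2.7): "Sub-group analyses will be planned for patients who used other long-term electrocardiographic monitors, such as ICM". This subgroup is the only separation planned, and its content is not described.

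Study design (2.1) describes a single observational registry without a comparison group.

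**The concern.** The question concerns one detection method, while the outcome counts AF however it was found. An ICM can record AF whether or not a therapist feels an irregular pulse, and an ECG for chest symptoms does not depend on a pulse finding. Without a control group, the route by which each case was first found is the only basis in this design for crediting a case to the pulse checks.

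At stake is the claim that the Discussion hopes to support: that pulse checks in rehabilitation hospitals are useful for detecting AF and starting anticoagulation. If the unrestricted proportion is read as the result of pulse checks, the yield may look better than it was. Timing of detection would likewise mix device, symptom and pulse-check detection times. The anticoagulation proportion in 2.4 depends on the same cases.

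**Working it through.** **The plan's own figure.** The only design number is the sample size of 1000 (2.6), taken from the previous year's admissions. No AF rate, precision or power accompanies it, so there is nothing to reproduce. Every rate below is an assumption used to show a range.

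**Notation.** N = 1000; f = share of patients with an ICM; q = share of ICM carriers in whom AF is detected; p = share of the other patients whose AF is found through a pulse check; s = share of the other patients whose AF is found only through a symptom ECG.

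Unrestricted proportion = f·q + (1 − f)·(p + s)

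Difference from the pulse-check yield p = f·(q − p) + (1 − f)·s

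**Step 1: ICM route alone (s = 0, p = 2%).**

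| | f | q | ICM AF | Pulse-check AF | Total | Proportion | Difference from 2% |
|---|---|---|---|---|---|---|---|
| Low | 5% | 5% | 1000 × 0.05 × 0.05 = 2.5 | 950 × 0.02 = 19 | 21.5 | 2.15% | 0.15 points |
| High | 10% | 15% | 1000 × 0.10 × 0.15 = 15 | 900 × 0.02 = 18 | 33 | 3.3% | 1.3 points |

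If p varies from 1% to 3%, the ICM share of all AF runs from 2.5/(2.5 + 28.5) = 8% to 15/(15 + 9) = 62.5%.

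**Step 2: why Step 1 is an upper bound for this route.** It treats every ICM case as one to which pulse checks contributed nothing. If half of the 15 cases in the high row were also felt at a pulse check, pulse-check-positive AF would be 18 + 7.5 = 25.5 per 1000, or 2.55%. The gap to 3.3% shrinks to 0.75 points.

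**Step 3: symptom route alone (f = 0).** With p = 1% and s = 1% the unrestricted proportion is 2.0%, and half of the cases are not from pulse checks. With p = 3% and s = 1% it is 4.0%, and a quarter are not. An ICM subgroup leaves this component untouched.

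**Step 4: both routes, wide range.** Take f = 0-20%, q = 5-20%, p = 1-3% and s = 0-1%. The share of AF from other routes runs from 0% (f = 0, s = 0) to 86% (f = q = 20%, p = s = 1%: ICM 40, symptom 8, pulse 8; 48/56). A middle case with f = q = 10% and p = s = 1% gives ICM 10, symptom 9 and pulse 9. That is 2.8% overall against 0.9% from pulse checks, with 19/28 = 68% of cases from other routes.

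The unrestricted figure is therefore compatible with AF found wholly by pulse checks or mostly by other means. It does not identify the quantity that the Introduction names.

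**The case against.** The strongest reply is that pooling is inferred. No sentence says that ICM-detected AF will be credited to pulse checks. The Introduction speaks of detection by pulse testing, 2.4 places the outcome next to the pulse-check-then-ECG pathway, and 2.7 could be shorthand for that. The flowchart is not shown. A reader might infer that the plan deliberately pools routes, but the text supports only that the outcome is not restricted. What survives is that, as worded in 2.4 and 2.7, AF from any route qualifies.

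Second, the ICM subgroup deals with part of the problem, and an article may leave its details to the full protocol. That is fair. But a subgroup analysis does not by itself take ICM carriers out of the main proportion, and it does not separate symptom-ECG cases in everyone else.

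Third, the bias could be negligible. With few ICM carriers and few symptom ECGs it is, and the article does not say whether device data are read during the stay. This stands, so overstatement is possible but not shown.

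Three further readings are tempting but unsupported:

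- *Route of detection is not recorded.* Table 2 names no route, but it also omits AF date, ICM use, echocardiography and brain imaging, all of which 2.7 needs. It cannot be read as the full case report form.
- *Patients' own pulse-taking is a further route.* Section 2.3 says that registered patients were taught palpation, but the next sentence turns to training therapists and the wording may be loose. Nothing says that a patient's own finding leads to an ECG.
- *The study must estimate sensitivity against ICM.* The article states no such objective, and precision would probably be poor.

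**Conclusion.** The point holds in a limited form. The stated aim is the rate and timing of AF detection by pulse testing; the stated outcome is AF detected by any route, in an uncontrolled cohort with at least two other routes. The outcome as worded cannot identify the pulse-check yield and may overstate it.

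The size is unknown. Under the assumed 5-10% ICM carriers with 5-15% AF, a 2% yield would be reported as 2.15% to 3.3%, an upper bound for the device route. Symptom ECGs would add to this by an amount that the documents do not allow one to estimate. Severity is should-fix, with moderate confidence: the mismatch is plain in the text, but its numerical effect rests wholly on assumed rates.

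**What to change.** 1. Define the main detection proportion, and its timing, as AF first identified on an ECG triggered by a therapist pulse check, in patients without an ICM or other long-term monitor. Report it with a 95% CI.
2. Record, or abstract from records, the first route of detection for every AF case (therapist pulse check, chest symptoms, ICM or other monitor, other). Report all AF by route, in all patients, beside the main figure.
3. Word the conclusion as the yield of pulse checks. Without a control group it is not evidence of added detection. Some AF first found on a symptom ECG might later have been felt at a pulse check, so a first-route yield leans slightly low; the breakdown by route lets the reader judge this.
4. Optionally, describe pulse-check findings against ICM-confirmed AF in ICM carriers, with an exact CI and a plain statement of its imprecision. If half of the cases were caught, the exact 95% interval would be about 19-81% with 10 ICM-positive patients and still 34-66% with 40.

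The cost is one data field and a few lines of analysis text. The headline proportion may be lower, the denominator loses the monitored patients (50 to 100 of 1000 under the 5-10% ICM assumption), and patients already enrolled since September 2022 need some retrospective abstraction. Section 2.4 already has the study office contacted for each identified AF, which should help. The definition should be settled before the results are examined.
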